Cervical cancer is an AIDS-defining malignancy, and HIV influences the risk for cervical cancer through multiple biologic pathways.^12^ HIV increases the incidence and persistence of infection with oncogenic human papillomavirus (HPV), the causative agent in cervical dysplasia cancer.^13-17^ HIV-infected women have a higher incidence and prevalence of cervical dysplasia and invasive cancer, a younger age of onset, present with more advanced malignancies and have lower survival rates than HIV-negative women.^11, 18-23^ Worsening HIV related immunosuppression is associated with more severe cervical lesions and disease progression.^24-26^ Recurrence of cervical lesions is much more common among HIV-infected than uninfected women,^27-30^ making follow-up essential for the prevention of invasive disease. The vast majority of women infected with HIV live in resource-limited settings with poor healthcare infrastructure, most notably in Sub-Saharan Africa. In these settings, limited access to cervical cancer screening programs puts them at even higher risk for cervical cancer related morbidity and mortality.^31^ HIV prevalence in Kenya was estimated to be between 4.9 and 7.3% at the end of 2007, with a prevalence in women aged 18-49 of 8.9%.^32, 33^ Before the widespread availability of anti-retroviral therapy, AIDS related deaths posed a much greater risk than cervical cancer. As the infrastructure for HIV treatment improves, women at highest risk for development of cervical disease are gaining access to the care and services that could facilitate cervical cancer prevention programs. HIV-clinics may represent the ideal setting for cervical cancer screening. To make an impact, screening and treatment strategies must be safe, low-cost and effective in HIV-infected women.

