Another important factor to consider in prioritizing the diagnosis of cervical dysplasia and cervical cancer in HIV-infected women is the potential for increased infectivity related to presence, diagnosis and treatment of cervical disease. This is especially important in countries such as Kenya, where HIV-prevention strategies remain paramount as healthcare resources and access to anti-retroviral therapy remain limited and the majority of infected individuals are in relationships with HIV-negative partners.^33, 55^ Understanding factors impacting HIV-transmission risk is essential to developing and implementing effective prevention strategies. The presence of HIV-1 in the genital tract plays a large role in the heterosexual and maternal-to-child transmission of HIV. ^56, 57^ The association between sexually transmitted infections (STIs) and increased risk of HIV transmission has been well studied and is thought to be partly attributable to increased levels of HIV-1 found in secretions of co-infected individuals.^58-60^ Herpes simplex virus type-2 co-infection is associated with the greatest increase in cervicovaginal HIV-1 shedding, even in the absence of genital ulcers.^61^ Increased shedding has also been seen with bacterial vaginosis,^62, 63^ *Chlamydia trachomatis*,^64^ *Neisseria gonorrhea*,^65^ *Candida* and nonspecific vaginitis.^66, 67^ Despite the high prevalence of HR-HPV, cervical dysplasia and cancer in this population, remarkably little is known about the relationship between HR-HPV-related lesions, treatment of these lesions and HIV-1 genital shedding. One prospective study among 124 HIV-infected women showed an up to 4-fold risk of HIV-1 RNA in the genital tract among women with HR-HPV, with no significant relationship to CIN. Limitations to this study include a high prevalence (50%) of cervical and vaginal infections and no participants on anti-retroviral therapy. A later study by the same investigators showed a two-fold increased risk of HIV-1 shedding among women with CIN, after controlling for plasma levels of HIV, CD4+ count and vaginal infections.^68^ A better understanding of the impact of CIN on HIV-1 genital shedding may provide additional rational for implementing screening programs in populations at high-risk for both cervical cancer and HIV transmission.

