**HYPOTHESES (NULL)**

1. VIA, VILI and p16^INK4a^ will perform equally well as screening tests for cervical cancer in HIV-infected women.
2. Women with CIN2/3 will have the same frequency and quantity of HIV-1 RNA detected in their genital secretions as women without CIN2/3.
3. Women treated with LEEP will have the same quantity of cervicovaginal HIV-1 RNA detected pre- and post-treatment and up to 14 weeks after the procedure.

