We propose a ***cross-sectional*** study to evaluate this specific aim. Each participant will undergo a VIA or VILI with specimen collection for p16^INK4a^ and HR-HPV and colposcopy by a different clinician during a single clinic visit. The study clinician performing the colposcopy will be blinded to the results of the VIA or VILI. For women in the VILI arm, the colposcopy will be performed first in order to eliminate any interference with colposcopy interpretation from the iodine staining. Biopsy decisions will be made at the time of colposcopy, but deferred until after the VILI. Any woman with cervical lesions suspicious for dysplasia seen at the time of colposcopy will undergo biopsy. Colposcopy will be used as the reference standard for presence or absence of CIN2/3, with biopsy results being the final diagnosis when available. Women with a normal colposcopy without biopsy will be considered to have no disease.Specific Aims 1, 2, 2a and 2b)

We propose a **prospective cohort** study using a subset of women identified from the cross-sectional study in Specific Aims 1 and 2a to evaluate specific aim 2c during a one-year follow-up visit. We will recruit women for this follow-up study who participated in the pilot p16^INK4a^ ELISA study (Aim 2a) and had normal colposcopy or CIN1. In a single visit, each participant will undergo a VIA with specimen collection for p16^INK4a^ and HR-HPV followed by colposcopy and biopsy if needed.

We propose a ***case-control*** study to measure and compare the presence and quantity of HIV-1 RNA in the cervicovaginal specimens of women with biopsy-confirmed CIN2/3 (cases) and age-matched women without evidence of cervical disease as measured by negative VIA (controls). We will compute the odds ratio for HIV-1 detection and compare log transformed mean viral loads between cases and controls. (Specific Aim 3)

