**Specific Aim 3:**

- Presence and quantity of HIV-1 RNA viral load in cervicovaginal secretions at the time of VIA/colposcopy. HIV-1 quantity will be expressed as log copies per microliter (µL) of vaginal fluid.

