**Specific Aims 2c:** To compare the rate of detecting CIN2/3 at one-year follow-up between women with normal or increased levels of p16^INK4a^ at baseline, we will use the Pearson’s chi-square test to investigate any significant differences in the proportions. Based on our sample size calculations, we aim to have 80 percent power with a two-sided alpha of 0.05. To compare the rates of developing CIN2/3 at one-year follow-up between women with persistently elevated p16^INK4a^ compared to those with only one elevated measurement, we will also use the Pearson’s chi-square test to look for statistically significant differences in proportions of CIN2/3 in the two groups.

**Specific Aim 3:** To compare the presence and magnitude of HIV-1 genital shedding between women with and without cervical dysplasia we will compute the odds ratio of HIV-1 detection in genital secretions with 95% confidence intervals. Multivariate analyses will be performed using logistic regression to control for demographic and clinical confounders. Potential confounders include WHO stage of HIV disease, CD4+ count, plasma HIV-1 viral load, opportunistic infections, previous STIs and current use of anti-retroviral therapy.

**Specific Aim 4:** The goal of specific aim 4 is to determine the magnitude and duration of increased HIV-1 genital shedding that occurs after treatment with LEEP. Observed time trends in log copies of genital HIV-1 RNA will initially be evaluated via exploratory analyses of longitudinal measures based on scatter plot smoothing methods. Results will allow us to assess possible nonlinearities in trends, as well as investigate differences in results between subgroups of interest. The subgroups we are looking at include participants on HAART and who have CD4+ counts below 200. Further analyses will focus on estimation of post-LEEP changes from baseline levels in log copies of HIV-1 RNA using linear mixed effects regression methods. The primary predictor will be time on study (measured in weeks post-treatment). Initial models will include separate coefficients for each week of observation post-treatment (2, 4, 6, 10 and 14). Hypothesis 2 will be addressed directly via tests constructed about these coefficients. We will also explore the effect on results of adjustment for selected covariates, including demographic characteristics and baseline descriptors of participant health status.

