**Serum Viral Load Testing ($3,100)**

Viral load testing is available through a clinical and research facility affiliated with the University of Nairobi and University of Washington in Nairobi at $31.00 per test. All 100 women in specific aims 1 and 2 will have baseline serum viral load testing. Total: 100*31=$3,100.

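### Aim 3 names quantity of genital HIV-1 RNA as an outcome but gives it only an unadjusted comparison of mean log viral loads; the one adjusted model serves detection alone

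*Protocol*

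**What the plan says.** Only the protocol is at hand.

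- **Quantity is an outcome.** Null hypothesis 2 states: "Women with CIN2/3 will have the same frequency and quantity of HIV-1 RNA detected in their genital secretions" as women without CIN2/3. The outcome list for Specific Aim 3 reads: "Presence and quantity of HIV-1 RNA viral load in cervicovaginal secretions at the time of VIA/colposcopy", in log copies per microlitre.
- **Quantity analysis.** Study Design, Specific Aim 3: "We will compute the odds ratio for HIV-1 detection and compare log transformed mean viral loads between cases and controls". No covariates are named.
- **Adjusted analysis.** Statistical Analysis, Specific Aim 3, opens by announcing a comparison of both presence and magnitude. It then gives the detection odds ratio with a 95% confidence interval and adds: "Multivariate analyses will be performed using logistic regression to control for demographic and clinical confounders".
- **Named confounders.** The same paragraph: "Potential confounders include WHO stage of HIV disease, CD4+ count, plasma HIV-1 viral load, opportunistic infections, previous STIs and current use of anti-retroviral therapy".
- **Background.** "Worsening HIV related immunosuppression is associated with more severe cervical lesions and disease progression". An earlier study of CIN and shedding is reported as finding a two-fold increase "after controlling for plasma levels of HIV, CD4+ count and vaginal infections".
- **Design controls.** Aim 3 women must have been on ARVs for at least 6 months with adherence above 90%. Laboratory evidence of cervical or vaginal infection excludes them. Controls are matched on age.
- **Data held.** CD4+ counts come from routine charts (Study measurements). CD4+ count and WHO status are listed under Predictor Variables, but plasma viral load is not. The Budget Justification funds 100 women who "will have baseline serum viral load testing", but assigns them to specific aims 1 and 2.

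**The concern.** A logistic model of detected versus not detected cannot produce an adjusted difference in log viral load. As the text stands, the frequency half of Aim 3 has confounder control and the quantity half has none, although the protocol's reason for adjusting applies equally to both. If cases have more advanced or less suppressed HIV than controls, part or all of a difference in mean log genital RNA could reflect that rather than CIN2/3. The two halves of the aim could also disagree simply because one is adjusted and the other is not.

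A second, smaller loss is precision. If plasma viral load predicts genital viral load, leaving it out widens the interval at a fixed 50 per arm.

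**Working it through.** **1. The plan's own figure.** The sample size section gives 46 per arm (50 enrolled) for a difference of about 25 points in detection, with 80% power and two-sided alpha 0.05. The unpooled two-proportion formula is

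n = (1.96 + 0.842)² × [p1(1−p1) + p2(1−p2)] / (p1−p2)².

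- 81% vs 55%: 7.85 × (0.154 + 0.248) / 0.0676 = 46.6, so 47. This matches 46 closely.
- 40% vs 17%: 7.85 × (0.240 + 0.141) / 0.0529 = 56.5, so 57.

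The 46 therefore reproduces with the more favourable pair of rates. It concerns detection only; the protocol has no sample size for quantity, and this point does not rest on the 46.

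**2. Which analysis serves which outcome.**

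| Outcome | Unadjusted analysis | Adjusted analysis |
| --- | --- | --- |
| Presence | Odds ratio with 95% CI | Logistic regression |
| Quantity | Difference in mean log viral load | None stated |

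By contrast, the Aim 4 paragraph of the same section names linear mixed models for log RNA and foresees covariate adjustment.

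**3. What the unadjusted comparison can detect.** The SD of 1.7 log is borrowed from the Aim 4 calculation; Aim 3 gives none.

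SE = 1.7 × √(2/50) = 0.34 log. Detectable difference at 80% power = 2.80 × 0.34 = 0.95 log (0.96 with the t distribution).

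**4. Effect of confounding when CIN2/3 itself has no effect.** Spurious difference b = slope of genital on plasma log RNA × case-control gap in plasma log RNA. The document gives neither, so both are assumed.

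False-positive rate = Φ(−1.96 + b/0.34) + Φ(−1.96 − b/0.34).

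| Slope | Gap (log) | b (log) | b/SE | Rate, normal | Rate, t-test |
| --- | --- | --- | --- | --- | --- |
| 0.3 | 0.5 | 0.15 | 0.44 | 7.3% | 7.2% |
| 0.5 | 0.5 | 0.25 | 0.74 | 11.4% | 11.3% |
| 0.5 | 1.0 | 0.50 | 1.47 | 31.3% | 30.8% |

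Over slopes of 0.3 to 0.7 and gaps of 0.2 to 1.0 log, b runs from 0.06 to 0.70 log and the rate from 5.4% to 54%.

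**5. Precision.** With assumed correlation ρ between covariate and outcome, the residual SD is 1.7 × √(1−ρ²). Power at 0.96 log rises from 80% to 84% (ρ = 0.3), 86% (0.4), 90% (0.5) or 94% (0.6). At ρ = 0.5 the detectable difference falls from 0.96 to 0.83 log.

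**6. A limit on steps 3 to 5.** At the detection rates quoted from the CIN study, 40% and 17%, arms of 50 would yield about 20 and 8 or 9 measurable values (50 × 0.40 = 20; 50 × 0.17 = 8.5). Most values would be undetectable. The normal-theory figures show order of size only.

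**7. A hint within the document.** For that study, 40% vs 17% gives a crude odds ratio of (0.40/0.60)/(0.17/0.83) = 3.25, beside a reported 1.86. That would fit an association that shrinks on adjustment. However, the protocol does not label 1.86 as adjusted, so this is no more than a hint.

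**The case against.** The strongest reply is that this is silence, not error. The Study Design sentence does not say the comparison of means is unadjusted or final, and a covariate model for a second outcome could sit in a statistical analysis plan not shown here. It is true that the protocol does not rule out adjustment. But it announces an analysis of presence and magnitude together, names the adjusted method, and the method it names cannot serve magnitude. That is worth correcting where it stands.

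A reader might infer that the quantity result *is* confounded, or that the protocol says the groups will differ. It does not. The statement on immunosuppression is general background, the listed factors are potential confounders, and the earlier study is said to have controlled for plasma HIV and CD4+ count, not to have needed to. Restriction to adherent women on ARVs, exclusion of infections and age matching all narrow likely differences, although none balances CD4+ count or plasma viral load.

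A reader might also infer that raw viral loads are averaged, or that both main covariates are certainly in hand. The values are log-transformed. CD4+ count is secure, but plasma viral load rests on a budget line labelled for other aims. Linking it to Aim 3 because 100 equals 50 + 50 is plausible but not stated.

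Finally, quantity is the lesser half of the aim. Hypothesis 3 and the sample size rest on detection, and Aims 3 and 4 are described as preliminary to a larger trial. This limits the consequences, but quantity remains in the aim, the null hypothesis and the outcome list.

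**Conclusion.** The point holds in this form: the only stated analysis of quantity is unadjusted, the only adjusted model cannot apply to it, and the protocol names the factors that leave it open to confounding. The document does not support the stronger claim that the result will be biased, or by how much. The range of 7% to 31% assumes spurious differences of 0.15 to 0.5 log, an SD borrowed from Aim 4, and approximately normal data; with a small plasma gap the effect is close to nil (5.4%). The precision gain is likewise conditional. It reaches about 5 points of power only at a correlation near 0.4 or more, and would be smaller if most women on ARVs have undetectable plasma virus. The change should be made because it is cheap and puts both halves of Aim 3 on the same footing.

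**What to change.** In Statistical Analysis, Specific Aim 3, name as the quantity analysis a regression of log genital HIV-1 RNA on case/control status that:

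- uses a short covariate set fixed in advance: CD4+ count and plasma log HIV-1 RNA, plus age or the matched sets;
- uses a method suited to undetectable values, for example censored (Tobit) regression;
- reports the adjusted difference with its 95% confidence interval as the quantity result, with the unadjusted difference as descriptive.

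Reconcile Predictor Variables and the serum viral load budget entry with the Aim 3 confounder list, so that plasma viral load is clearly collected for the 100 Aim 3 women. State when blood is drawn: the enrollment visit lists genital specimens only, and cases are identified only at their later follow-up visit.

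The cost is a short paragraph, a few degrees of freedom among 100 women, and a rule for missing plasma values. If few genital values are detectable, the censored model will lean on its distributional assumption and the interval will be wide. No added visit follows from the analysis itself, and no added test if the 100 budgeted serum tests are indeed for these women.

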- **Cervical specimens for HIV-1 RNA detection and quantification:** A study clinician will place 3 Sno-Strip™ wicks (Chauvin Pharmaceuticals Ltd., Essex, England) in the posterior fornix of the vagina and allowing the vaginal fluid to absorb to each strip. The vaginal fornix was chosen instead of the endocervix because vaginal Sno-Strips provide a more reproducible detection and quantification of HIV-1 RNA than endocervical Sno-Strips, especially in the presence of endocervical mucus and debris.^88^ We also want to avoid disruption of the post-procedure healing cervix. The Sno-Strips will be placed in NASBA buffer and processed by the on-site laboratory within 2 hours of collection. After this time they will be placed in the –80º freezer until transport to the ARI-UCSF Laboratory of Clinical Virology for viral load testing.
- **Vaginal specimens for yeast, bacterial vaginosis and trichomonas:** After cervical specimen collection is complete, the study clinician will use a cotton swab to collect any fluid or discharge from around the posterior fornix and vaginal walls and place it in a test tube with 2cc of normal saline. The clinician will read the specimen immediately after the study examination and discard it after recording the results.

**Visual Inspection with Acetic Acid:** After identification of the cervical anatomy, including the squamo-columnar junction, the clinician will apply 5% acetic acid. After one to two minutes, the clinician will examine the cervix again to interpret the results of the VIA.

VIA will be defined as negative if the following findings are present:

- circumferential identification of the squamo-columnar junction (SCJ)
- no aceto-white lesions or faint, ill-defined, bluish white lesions at the SCJ or aceto-white lesions far away from the SCJ

VIA will be defined as positive if the following findings are present:

- well-defined, opaque aceto-white lesions touching the SCJ or surrounding the external os
- large circumferential aceto-white lesions covering the external os,
- pre-existing condyloma or leukoplakia which turns intensely white after application of acetic acid

**Visual Inspection with Lugol’s Iodine:** After identification of the cervical anatomy, including the squamo-columnar junction, the clinician will apply Lugol’s Iodine. After staining is noted in the transformation zone, the clinician will examine the cervix again to interpret the results of the VILI.

VILI will be defined as negative if the following findings are present:

- circumferential identification of the squamo-columnar junction (SCJ)
- complete iodine uptake around the SCJ and into the transformation zone

VILI will be defined as positive if the following findings are present:

- well-defined, iodine yellow areas within or immediately surrounding the SCJ
- patchy areas of missing iodine uptake in the transformation zone

In order to maintain strict blinding of study clinicians, the results of the VIA or VILI will not be shared with the participant until after the colposcopy has been performed. The study clinician performing the VIA or VILI will leave the room with the data collection form containing the test results before the second clinician enters the room to perform the colposcopy.

**Colposcopy and biopsy:** Colposcopy will take place by a second, blinded study clinician immediately after VIA or VILI. Colposcopic exam will be done in accordance with the International Federation for Cervical Pathology and Colposcopy (IFCPC) guidelines,^89^ and will include sequential evaluation using green filter, acetic acid and Lugol’s Iodine. Findings on colposcopy that are suggestive of a CIN2/3 or worse lesion will prompt a colposcopically-guided biopsy. A normal colposcopy will be considered a final result indicative of no disease. (What about CIN1?) *the hgcin should have gotten a biopsy. The clinician performing the colposcopy will be assisted by the study nurse, who will also be blinded to the results of the VIA. They will have access to the participant’s clinical record, but not to the VIA results. Colposcopy findings will be recorded on a separate data collection form. After the colposcopy findings have been recorded the results of both tests will be discussed with the participant, including implications for treatment and future screening.

Study visits (Appendix E)

Specific Aims 1, 2a, 2b and 3:

**Enrollment visit**: Informed consent, VIA/VILI, colposcopy and genital specimen collection for HIV-1 viral load, HR-HPV, p16^INK4a^, and STI testing will take place during a single visit. If indicated by abnormal findings at colposcopy, participants will undergo directed biopsy at the time of colposcopy for diagnosis of cervical dysplasia. No biopsies will be performed solely for study purposes. Follow-up appointments will be made for two to four weeks after enrollment visit among participants undergoing biopsy. This visit will comprise the total study participation for subjects in the cross-sectional study who have negative colposcopy. They will be scheduled for their regular clinical follow-up as indicated by their health status.

For specific aim 3, matching of controls to cases will take place after cases have been identified. The inclusion criteria for the case-control study depend on test results that are not readily available (negative STI testing and biopsy results positive for CIN2/3), therefore cases will not be identified until their follow-up visit. In order to minimize confounding secondary to biopsy collection, HIV-1 viral load specimens for cases and controls will be taken during the single study visit for specific aims 1, 2 and 3. Samples will be kept in the on-site –80º freezer until the time that cases are identified, at which time samples from women ineligible for enrollment will be discarded.

**Follow-up Visits at day 2 and 7:** Women who underwent cervical biopsy and are eligible for S.A. 3a will return on day 2 and 7 following biopsy, during which time they will undergo a sterile speculum exam with specimen collection for HIV-1 RNA.

**Results Visit (for clinical care, not required for study participation):** Women undergoing cervical biopsy will be scheduled for a follow-up visit in two to four weeks. They will receive their biopsy results from the study clinician, and may be offered enrollment into the post-LEEP HIV-1 shedding study if eligible.

Specific Aim 2c:

**Single Follow-up visit**: Informed consent, VIA, colposcopy, and cervical specimen collection for HR-HPV, and p16^INK4a^ will take place during a single follow-up visit for women who previously underwent p16^INK4a^ testing and meet criteria for these specific aims. If indicated by abnormal findings at colposcopy, participants will undergo directed biopsy at the time of colposcopy for diagnosis of cervical dysplasia. No biopsies will be performed solely for study purposes.

Specific Aim 4 (7 study visits):

**Enrollment:** Women returning for their biopsy results who have CIN2/3 will be offered treatment with LEEP at this visit, as is the current clinic protocol at FACES. Recruitment and enrollment into the post-LEEP HIV-1 shedding study will take place at this visit. Women who meet eligibility criteria will be offered enrollment. Informed consent for this study will be obtained during this visit, and participants will be assigned a study ID number. A follow-up visit schedule will be made.

**Follow-up Visits at 1, 2, 4, 6, 8, 10 and 14 weeks:** Participants will undergo a brief interview followed by a sterile speculum exam with specimen collection for genital HIV-1 RNA.

Study measurements

Individual participant data, including demographic and clinical information will be collected from the paper medical record using study-specific data collection forms. Individual and de-identified aggregate data will be abstracted from the electronic medical record system (OpenMRS) in place at FACES. Participants will all be enrolled in FACES for care of their HIV disease; as part of this care, they have regular laboratory monitoring of CD4+ counts, hemoglobin levels and basic serum chemistries. Laboratory data for the study, apart from histology and HIV-1 RNA specimens, will be obtained from their FACES charts, and will not be collected independently for the study.

